### Main actors in the program

This trial will include three primary groups of participants. The first group will be the beneficiaries of the intervention, including pregnant women and mothers of infants and their newborn babies or children aged 0–24 months. The second group will be the *i-MoMCARE* facilitators (level 1 and 2 technology support personnel) assisting digital health technology users. The third group will include VHSGs and HC staff—the mobile application and web interface users.

#### i-MoMCARE facilitators

Two facilitators, the University of Health Sciences (UHS) staff, will provide technical support to the digital health technology users at either level 1 or level 2. The technical support at level 1 will include (i) collecting user requests and data, (ii) answering users’ phone calls (first contact), (iii) responding to users’ text messages, (iv) creating tickets for level 2 support, (v) providing features of the *i-MoMCARE*, and (vi) solving logistical and technical problems, such as password issues, menu navigation, verification of hardware and software, installation issues, and setup. The technical support at level 2 will involve more in-depth troubleshooting, including (i) using the facilitator dashboard available through the *i-MoMCARE* web interface for monitoring adherence to the *i-MoMCARE* intervention by using process indicators and undertaking housekeeping functions of the web interface, which includes dealing with the migration of pregnant women or mothers, duplication in registering cases, and verification of deaths reported by VHSGs and (ii) making occasional field visits to provide ongoing training, supervision, and encouragement to enhance motivation to poor performing VHSGs and sending a short message service (SMS) text to VHSGs and HC staff to inform them about high-risk cases diagnosed by VHSGs [18].

#### Village health support groups (VHSGs)

VHSGs are usually elected by their community members and based in the community under the HC’s coverage. VHSGs are community-based health volunteers with limited education; some do not even have education beyond primary school [28]. They will be the primary implementers of the *i-MoMCARE* intervention. They will communicate with the beneficiaries directly to narrow the gap in the knowledge of maternal, newborn, and child health and refer pregnant women and children to the nearest HC when necessary. One HC serves approximately 10 villages, and one village has one or two VHSGs serving 100 households or more. We will select 20 VHSGs (two VHSGs per village) for each HC in the intervention and control arms (200 from each arm). All VHSGs in the intervention and control arm will undergo MCH-related refresher training before the intervention. Only VHSGs in the intervention arm will be equipped with the mobile application.

#### Health center staff

We will invite 20 HC staff (two from each) working closely with VHSGs and involved with data management at the HC in the intervention arm to participate in the study. HCs usually provide minimum package activities, including ANC, deliveries, PNC, immunization for children and women, neonatal and child care, nutrition, communicable and non-communicable disease services, health education and promotion, and outreach activities [25]. VHSGs assigned to the intervention arm will conduct home visits and provide care, such as diagnosis, referral, counseling, and administering drugs, to mothers with complications who cannot visit the HCs. The HC staff will supervise and support VHSGs and verify VHSGs’ performance reports on such activities. One of the two selected HC staff for each HC will serve as a site coordinator providing feedback on VHSGs’ counseling and technical skills, organizing small group meetings with VHSGs, and facilitating the selection and replacement of VHSGs in the HC’s catchment areas. The site coordinators will further assist VHSGs who are poorly functional because of limited skills and knowledge, delays in payments, illness of family members, lack of family support, or other social barriers.

### Theory of change

The logic model outlined in Fig. 3 describes how *i-MoMCARE* will attain its goal of reducing MMR and IMR in rural Cambodia. It comprises four major components—input, activities, outputs, and outcomes. Input refers to human and financial resources available for project implementation. The human resources will include faculty and researchers from the Saw Swee Hock School of Public Health of the National University of Singapore (NUS-SSHSPH), the University of Health Sciences (UHS), NMCHC, and Argusoft, an international technology service provider. The project receives funding from the Bill & Melinda Gates Foundation (BMGF). The activity column illustrates how we will pool human and financial resources to generate outputs presented in the output column. The activities include staff recruitment, study protocol submissions for ethical approval, qualitative formative studies, and collaboration with Argusoft and local implementers. We will translate the outputs into short-, medium-, and long-term outcomes.

**Fig. 3 Fig3:**
[figure not shown]
Logic model of the Innovative Mobile Technology for Maternal and Child Health Care (*i-MoMCARE*) intervention. BMGF, Bill & Melinda Gates Foundation; *i-MoMCARE*, Innovative Mobile Technology for Maternal and Child Health Care; ImTeCHO, Innovative Mobile-phone Technology for Community Health Operations; IRB, institutional review board; NECHR, National Ethics Committee for Health Research; NMCHC, National Maternal and Child Health Center; MCH, maternal and child health; NUS-SSHSPH, Saw Swee Hock School of Public Health of the National University of Singapore; UHS, University of Health Sciences; VHSG, village health volunteer group. The short-term outcomes are measured among mothers of children under 2 years or pregnant women, while the medium-term outcomes are measured among children under 2 years old

We expect that *i-MoMCARE* will improve pregnant women’s knowledge about maternal and young infant care and attitudes toward using maternal, newborn, and child health services. As a result, it will enhance health-seeking behaviors and MCH outcomes indicated by the MCH composite coverage index illustrated in the subsection below. The ANC, PNC, and facility-based delivery rates are also expected to increase in the medium term. Achieving short- and medium-term outcomes would reduce MMR and IMR in the long term.

### Intervention

#### Phase 1: Single-arm pilot of i-MoMCARE

A single-arm pilot study will be conducted in the last quarter of year 1 to ascertain the reliability and success of its deployment. The initial stage will include three steps: (I) identifying gaps in MCH standard care, (II) identifying components of digital health for addressing the gaps in MCH standard care, and (III) piloting the operational delivery of the intervention.

##### Identifying gaps in MCH standard care

We will conduct a literature review and a consultation meeting with NMCHC. We will also conduct key informant interviews (KIIs) with stakeholders from NMCHC, NGOs (the World Health Organization [WHO] and United Nations Population Fund [UNFPA]), a provincial health department (PHD), and an operational district. KII topics will include digital health literacy, digital health policies, health technology assessment (HTA), and challenges and recommendations. We will conduct in-depth interviews (IDIs) with VHSGs and HC staff and focus group discussions (FGDs) with pregnant women and new mothers. IDI topics will include job scope, support, training, and barriers and challenges in their work. FGD topic guide will consist of questions about their experiences in accessing MCH services and interactions with VHSGs. Besides the KIIs with NMCHC and NGOs, we will interview stakeholders in the province where the pilot intervention will be implemented. An estimated number of KIIs, IDIs, and FGDs are presented in Table 2. The data collection will be carried out until information saturation is reached. We will include women who are pregnant at the time of recruitment, have the youngest child younger than 24 months old, have lived in the village in the past 6 months, have received pregnancy-related services from HCs, and have received ANC and PNC support from VHSGs.

**Table 2 Tab2:** Number of qualitative interviews for gap analysis

Participant	KIIs	IDIs	FGDs
National maternal and child health center	1		
Non-governmental organizations	2		
Provincial health departments	1		
Operational districts	1		
Health center directors	3		
Health centers		6	
Village health volunteer groups		6	
Pregnant women and new mothers			3^a^
Total	8	12	3

*FGD* Focus group discussion, *IDI* In-depth interview, *KII* Key informant interview

^a^With 6–8 women in each group

##### Identifying technology components to address the gaps in standard care

We will identify technology components expected to tackle gaps in standard care based on consultations with Argusoft. A mobile application and web interface will be developed featuring functions that will assist the VHSGs in increasing MCH coverage and aid VHSGs and midwives in facilitating care for eligible mothers, newborns, infants, and children with complications. Various housekeeping functions, including troubleshooting, will be identified at this stage with support from Argusoft for optimal delivery.

##### Piloting operational delivery of i-MoMCARE

For piloting the *i-MoMCARE* implementation, we will select 50 VHSGs from five HCs (10 VHSGs per HC) and two HC staff under one selected operational district from one province. To avoid contamination, we will carry out the pilot in a province other than the provinces chosen for the intervention and control. The VHSGs and HC staff will be recruited for a 3-month pilot intervention and trained to use the mobile phone application and web interface. The pilot intervention will start with the preparation, training, and on-the-ground mentoring of VHSGs and HC staff on using the mobile phone application and a web interface for stabilizing and maintaining MCH service delivery. As shown in Table 3, we will assess the acceptability and feasibility of the pilot intervention through IDIs with VHSGs and HC staff who used the mobile application and web interface during the pilot. We will also conduct FGDs with six to eight pregnant women and mothers of children younger than 2 years old. Challenges and barriers related to the intervention delivery will be identified through the pilot, IDIs, and FGDs. Furthermore, we will finetune the mobile application and web interface to monitor implementation and progress in collaboration with Argusoft.

**Table 3 Tab3:** Qualitative interviews after the pilot

Participant	In-depth interview	Focus group discussion
Health center staff	4	
Village health volunteer group	10	
Pregnant women and new mothers		2^a^
Total	14	2

^a^With 6–8 women in each group

#### Phase 2: Cluster randomized controlled trial

An open cluster randomized controlled trial will be conducted to evaluate the mobile application utilization and the intervention’s effectiveness in improving MCH service uptake and outcomes aided by the mobile application. We have estimated that approximately 200 VHSGs will be included in the intervention arm across five operational districts (ODs) in five provinces. Figure 2 shows a flowchart of VHSGs and the HC staff selection process for the intervention and control arms. Figure 4 illustrates the map of the 10 provinces proposed as study sites, five of which will be assigned to the intervention arm after randomly selecting one OD from each. We will randomly select two HCs covering approximately 10 villages from each OD. Two HC staff will be purposively selected from each HC in the intervention arm.

**Fig. 4 Fig4:**
[figure not shown]
Map of the study sites (each color represents a paired province)

The designated HC staff will receive a web interface application as their job aid for supervising VHSGs, including real-time information about VHSGs’ performance in the form of process indicators and MCH service coverage. The web interface will provide timely information and tools for HC staff to facilitate the monitoring and supporting of VHSGs by supporting HC staff in their daily tasks, such as high-risk patient tracking, low-supply inventory alerts, supply chain management, electronic health records, vital events tracking, and automatic calculation of performance-based incentives and motivation for VHSGs. Two VHSGs from each of the 100 villages (a total of 200 VHSGs) will receive the mobile application connected to their respective HC in the intervention arm. The mobile application will provide job aid to VHSGs to enroll eligible women and children, schedule and review home visits, report outcomes of pregnancies, conduct home-based newborn care, follow-up visits of complicated cases, and report information about deaths, emergencies, migrations, referrals, and services, by logging into the application installed on the mobile devices every day except for Sundays. The mobile application will also help with behavioral change communication via brief educational videos about danger signs in pregnancies and newborns to be shown to pregnant women. At endline, we will conduct a qualitative acceptability and feasibility assessment of the intervention by conducting IDIs with VHSGs and HC staff from the intervention arm and FGDs with six to eight eligible pregnant women and mothers of under-two children in the five HCs selected for the IDIs. Approximate numbers of IDIs and FGDs are shown in Table 4. The interviews will be conducted until saturation of the information is reached.

**Table 4 Tab4:** Qualitative interview at the endline

Participant	In-depth interview	Focus group discussion
Health center staff	10	
Village health volunteer group	10	
Pregnant women and new mothers		5^a^
Total	20	5

^a^With 6–8 women in each group

##### Control arm

As discussed in the study design, HCs in the control arm will be randomly selected from their ODs. The randomization process will be similar to those in the intervention arm. All villages under the HC’s catchment areas in the control arm will continue to receive MCH standard care provided by the government and NGOs and facilitated by VHSGs. VHSGs in the intervention and control arms will receive refresher training on maternal, neonatal, and childcare to avoid ethical issues that may arise and ensure that any change in outcomes in the intervention arm is due only to the *i-MoMCARE* intervention.

##### Criteria for discontinuing or modifying allocated interventions 

The intervention implemented in this study will be part of standard procedures endorsed by Cambodia’s national MCH program. We do not foresee discontinuation or modification of allocated interventions because the proposed activities will pose no more than minimal risk and not adversely affect participants’ welfare. Participation in the activities in the study will be voluntary, and the participants can withdraw from the study at any time.

##### Strategies to improve adherence to interventions

In this study, the implementing organizations will design and ensure that the intervention’s protocol is strictly followed. The medical procedures and laboratory tests conducted in the health facilities will not be part of this study and are in accordance with the national MCH guidelines. In addition, researchers from the National University of Singapore, which is not an implementing organization, will conduct regular supervision and interim analyses to ensure adherence to the study protocol.

##### Relevant concomitant care permitted or prohibited during the trial 

Due to the trial’s nature, no concomitant care would be specifically permitted or prohibited during the study. We will conduct the community-based intervention according to standard operating procedures in a “real-world” setting.

##### Provisions for post-trial care

Post-trial care will be provided in accordance with the standard care as defined in the national MCH guidelines under the purview of the NMCHC.

### Outcomes and measures

We have selected primary and secondary outcomes based on the study in Gujarat, India [18]; Cambodia’s National Guideline for Implementing the Service Package of Antenatal Care, Delivery, and Postnatal Care 2019 [29]; and consultations with the NMCHC. We have also selected other primary outcomes, such as the proportion of neonates/mothers visited at home by VHSGs within the first week of delivery and mothers receiving information regarding the danger signs of newborn illnesses, based on a previous formative study [30].

#### Primary outcomes

VHSGs will facilitate the primary outcomes of interest throughout the continuum of care, including (1) the proportion of neonates/mothers visited at home by VHSGs at least twice within the first week of delivery, (2) the proportion of mothers receiving information from VHSGs regarding danger signs of newborn illnesses within the first week of delivery, and (3) the MNCH composite coverage index, consisting of four dimensions, namely maternal care, neonatal care, infant care, young childcare, and care-seeking when having complications.

The MCH composite index was initially introduced by Boerma et al. [31, 32]. It captures a complete continuum of care of mothers and children by including four dimensions: family planning, maternal and newborn care, immunization, and treatment of children. Following Modi et al. [27], we will exclude family planning to focus more on the role of the VHSGs in evaluating the effectiveness of mobile health technology. The three components will be equally weighted. The index will be calculated using the following formula: MCH-CI = 1/3 (¼ APNC + ½ IMMU + 1/3 TREAT), where APNC denotes antenatal and postnatal care, IMMU denotes immunization among children, and TREAT denotes the treatment of children. The index will vary between 0 and 100, with a higher index score indicating a higher MCH coverage. We will use the MCH coverage index to evaluate the effectiveness of the intervention. We have conjectured that the coverage rate should be well above 60% to be meaningful since earlier estimates of the compelling national coverage of maternal health services (ANC and facility delivery) and sick childcare (diarrhea, pneumonia, and fever) in 2014 were 56.4% and 59.1%, respectively [33]. Another recent study using a slightly deviated measure of the mother and infant care continuum shows that the national coverage was 49.4% [34].

APNC will consist of four sub-components: (1) the proportion of mothers visited by VHSGs at least three times in the last pregnancy, (2) the proportion of mothers with at least four ANC visits in the last pregnancy and one tetanus vaccine injection, (3) the proportion of mothers delivered at a health facility (public or private), and (4) the proportion of mothers with at least three PNC visits in the last pregnancy. IMMU will consist of two sub-components: (1) the proportion of young infants aged 12–24 months fully vaccinated based on the national guideline with one dose of Bacillus Calmette–Guérin (BCG) vaccine for tuberculosis; three doses of polio vaccine given as oral polio vaccine (OPV), inactivated polio vaccine (IPV), or combination of OPV and IPV; three doses of diphtheria, pertussis, and tetanus (DPT) vaccine; and one dose of measles vaccine given as measles-rubella (MR) and (2) the proportion of young infants exclusively breastfed in the first 6 months. TREAT will consist of three sub-components: (1) the proportion of neonates with complications in the first month of the last delivery who seek care from VHSGs, (2) the proportion of infants aged two to 24 months with diarrhea in the last 2 weeks and receiving oral rehydration therapy (ORT) from VHSGs, and (3) the proportion of infants aged 2 to 24 months with acute respiratory infections in the last 2 weeks and seeking care from VHSGs.

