**Methods:**

i-MoMCARE, a two-arm cluster randomized controlled trial, will be conducted between 2022 and 2025. Five operational districts (ODs) have been randomized to an intervention arm and the other five ODs to the control arm. The intervention will last for 24 months. Around 200 VHSGs in the intervention arm will be equipped with a mobile application as a job aid and 20 HC staff with a web interface to improve support and supervision of VHSGs. The potential beneficiaries will include pregnant women, mothers, and children under 2 years old. We will measure the outcomes at baseline and endline. The primary outcomes will consist of a composite MCH index constructed from maternal and newborn care indicators, child immunization, and treatment of under-two children. Secondary outcomes will include coverage of selected MCH services. We will conduct the intention-to-treat and per-protocol analyses. We will conduct qualitative interviews with selected beneficiaries and stakeholders to evaluate the intervention’s acceptability, feasibility, and scalability. We will also conduct a cost-effective analysis using decision-analytic modeling incorporating a societal perspective that explores different time horizons, intervention effects, and when scaled up to the national level.

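### The abstract names one primary outcome and the methods name three; the sample size fits one, and the multiplicity rule shares alpha without saying which outcome decides the trial

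*Protocol article*

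**What the plan says.** All references are to the protocol article.

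- **Abstract, Methods:** "The primary outcomes will consist of a composite MCH index constructed from maternal and newborn care indicators, child immunization, and treatment of under-two children". No other primary outcome is named there.
- **Outcomes and measures, opening paragraph:** further primary outcomes were added on the basis of a formative study, among them "the proportion of neonates/mothers visited at home by VHSGs within the first week of delivery and mothers receiving information regarding the danger signs" of newborn illness.
- **Primary outcomes:** three numbered items. These are "1) the proportion of neonates/mothers visited at home by VHSGs at least twice within the first week of delivery", then "2) the proportion of mothers receiving information from VHSGs regarding danger signs of newborn illnesses within the first week of delivery", then "3) the MNCH composite coverage index, consisting of four dimensions". The same section later states: "We will use the MCH coverage index to evaluate the effectiveness of the intervention".
- **Sample size:** ICC 0.02, effect 13%, a coverage-index level of 70%, about 200 mothers per cluster, five clusters per arm, 95% confidence and 85% power. The result is 929 per arm (1858 in total), raised to 1951 for non-response. No baseline rate is given for either VHSG-contact outcome.
- **Analysis plan, quantitative data:** Bonferroni and a bootstrap method are to handle multiplicity over primary and secondary outcomes. No order of testing and no rule for the primary set is given.

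**The concern.** Which outcomes are primary, and how each is defined, is for the protocol to fix, and here its sections disagree on both.

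On number, a reader of the abstract expects one primary result and a reader of the methods expects three. On definition, a mother visited once in the first week counts under the introductory wording but not under the Primary outcomes wording. Danger-sign information from a midwife counts under the first but not the second.

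The design elements point in different directions too. The sizing and the effectiveness statement treat the index as the outcome that matters. The multiplicity rule treats the index as one of a family of endpoints that share the alpha. Both cannot hold at the stated power: either the index keeps the full 0.05, or it is tested at a smaller alpha and 85% no longer applies. At stake are the chance of detecting the planned effect on the index and a clear statement, before the data are seen, of which result answers the trial's question.

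**Working it through.** **1. Reproduce the stated sample size.** Inputs from the Sample size section: 0.70 versus 0.83 (reading 13% as percentage points), power 0.85, ICC 0.02, cluster size 200. The 95% confidence level is read as two-sided alpha 0.05.

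- Variance term: 0.70 × 0.30 + 0.83 × 0.17 = 0.3511
- n per arm without clustering: 0.3511 × (1.960 + 1.036)² / 0.13² = 186.5
- Design effect: 1 + (200 − 1) × 0.02 = 4.98
- n per arm: 186.5 × 4.98 = 928.9, i.e. 929; total 1858

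This matches the protocol. The sizing is therefore one comparison at 0.05 and contains no allowance for further primary outcomes.

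**2. Power of the same sample at a shared alpha.** The standard error of the difference is √(0.3511 × 4.98 / 929) = 0.0434, and 0.13 / 0.0434 = 2.997. Power is Φ(2.997 − critical value).

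| Endpoints sharing 0.05 | Alpha each | Critical value | Power |
|---|---|---|---|
| 1 | 0.05 | 1.960 | 85% |
| 3 | 0.0167 | 2.394 | 73% |
| 31 | 0.0016 | 3.154 | 44% |

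The 31 is three primary outcomes plus the 28 rows of Table 5 outside the process indicators (ANC 4, delivery 5, PNC 4, neonatal 5, young infant 6, young child 4). Several rows hold more than one proportion, so the true number could be higher.

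**3. Sample size needed for 85% power at 0.05/3.** 0.3511 × (2.394 + 1.036)² / 0.13² × 4.98 ≈ 1217.5 per arm, about 2435 in total before non-response, against 1858.

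These figures follow the protocol's own normal approximation. With ten clusters and a t reference on 8 degrees of freedom, the first two powers would be about 75% and 53%. The absolute levels are thus optimistic, but the loss from splitting alpha remains.

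**4. What the index contains.** The three components are equally weighted. If items are also equally weighted within components, VHSG contact enters through one of four antenatal/postnatal items (1/3 × 1/4 = 1/12) and all three treatment items (1/3). Together that is 5/12, about 42% of the index.

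**The case against.** Much can be said for the plan as written.

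- **The two added outcomes are deliberate and relevant.** The abstract's background states two aims, better VHSG performance and higher service coverage, and first-week visits and counselling speak to the first. This stands: they deserve a named place. It does not settle whether they rank equally with the index.
- **The looser wording is introductory.** It follows a 'such as', and the Primary outcomes section gives the full definitions. This is probably right, which makes alignment easy, but two visit thresholds remain in print.
- **A hierarchy or success rule may be in an analysis plan that is not shown.** True. But the disagreement over which outcomes are primary, and the mismatch between sizing and multiplicity rule, lie within this document.
- **The 70% baseline is for a different coverage index.** It has no VHSG-contact or treatment items, so the sizing supports a single index comparison without matching the primary index exactly. This also stands.

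Three stronger readings are tempting and are not supported. A reader might infer that the trial could be declared positive on intervention delivery alone; no section states such a rule, and effectiveness is tied to the index. A reader might infer that testing three primaries leaves the false-positive rate uncontrolled; the analysis plan provides Bonferroni and resampling. A reader might see the two added outcomes as tallies of tasks that the app schedules. They are proportions from a household survey in both arms. The app is described as a "job aid to VHSGs to enroll eligible women and children, schedule and review home visits", but for danger signs the text mentions only videos shown to pregnant women.

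**Conclusion.** The point holds as an inconsistency with a consequence for power. The sections disagree on whether there is one primary outcome or three, and on the wording of two of them. The sizing and the effectiveness statement fit a single deciding index, while the multiplicity rule does not give it that role. At the protocol's own assumptions, power for the planned 13-point effect falls from 85% to about 73% with three equal primaries, and to about 44% if some 31 endpoints share the alpha.

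These figures assume two-sided testing, plain Bonferroni, the normal approximation and success on any one outcome. A resampling adjustment would lose less where endpoints are correlated. If success required all three primaries, alpha would not need splitting among them, but power for the joint result would then have to be stated. The document specifies neither rule. The matter should be corrected and does not threaten the design.

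**What to change.** 1. Name the MCH composite index as the single deciding primary outcome, tested at 0.05, in the abstract, the Outcomes and measures paragraph, the Primary outcomes section and the registry entry.
2. Keep the two VHSG-contact proportions as secondary or subordinate outcomes, tested after the index with multiplicity control. Use the Primary outcomes definitions everywhere: at least two first-week visits, and information from VHSGs within the first week.
3. State in the analysis plan which endpoints the Bonferroni/resampling adjustment covers, with the index outside that shared alpha.
4. If the investigators prefer three co-equal primaries, say so in the abstract, state whether one or all must succeed, and restate the power at the adjusted alpha.

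The cost is wording in the protocol and registry, with no change to sample or data collection. The downside is the loss of a stand-alone primary claim for VHSG contact. The change also does not by itself isolate service coverage, because about 5/12 of the index (equal weights) is VHSG contact. Reporting the index components alongside the total would let readers see where any change arises.
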